### Instruments and outcomes

The primary outcome is the patients’ quality of life as measured by SF-36 [16] and the Minnesota Living with Heart Failure Questionnaire (MLHFQ) [17]. The SF-36 is a generic measure of health impairment, with scores ranging from 0 to 100: zero indicates the worst quality of life and 100 the best. The MLHFQ is specific for chronic heart failure and has 21 questions with scores ranging from 0 to 105: zero indicates best quality of life and 105 the worst. Quality of life is assessed at baseline and at 7, 13 and 19 months by the patients, or their main caregiver, within 7 days of their appointment with their GP. A score of < 24 on the MLHFQ signifies a good quality of life, a score between 24 and 45 signifies a moderate quality of life, and a score > 45 signifies a poor quality of life [18]. We will assess these cut-off scores to interpret results in clinical terms. We were unable to find published cut-off information for the SF-36 health scores.

The secondary outcomes are: all-cause and heart-failure-associated mortality; all-cause and heart-failure-associated hospitalization, number of days in hospital; the cumulative number of all cause death or HF hospitalizations and the cumulative number of days of hospitalisation; adherence with therapy; evolution of NYHA heart failure stage; evolution of treatment; and changes in weight and body mass index (BMI) at 19 months. We will assess guideline adherence of treatment at baseline and during the follow-up period. Patient adherence with therapy will be assessed by the patients themselves with a self-administrated questionnaire (validated in French) at baseline and at the end of follow-up period [19].

Should the planned follow-up appointment be missed, the reason is identified and categorised as follows: lost-to-follow-up; death; unable to attend for another reason. Hospitalisations and mortality will be recorded by GPs at each planned visiting case report form.

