### Control group

The GPs in the control group attend a three-hour information evening session to learn about the case report forms and the patients’ inclusion/exclusion criteria. Their patients have the same schedule for visits as those in the intervention group (at 1, 4, 7, 10, 13, 19 months) but without specific education intervention.

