#### Statistical analysis

The statistician will be blinded with regard to treatment allocation. The responses to the questionnaire will be entered into a customised Access database (Microsoft, Redmond, Wash, US). Analyses will be made using Stata, version 13 (StataCorp, College Station, Tex, US). If necessary, an adjustment to accommodate differences between the baseline characteristics of the groups will be made. Continuous data will be presented as mean ± standard deviation (SD). The comparisons between study groups will be analysed using Chi-square or Fisher's exact test for categorical variables, and Student's or Mann–Whitney tests for quantitative variables, with normality verified by the Shapiro-Wilk test and homoscedasticity by the Fisher-Snedecor test. The correlation between SF-36 and MLHFQ will be assessed using Pearson’s correlation coefficient. Hierarchical linear regression models with random-effects levels for practice, individuals within practices and repeated measurements per individual (slope and intercept) will be used to estimate the effects of the intervention on SF-36 and MLHFQ scores for the post-baseline time points. These models will include an interaction factor between both the randomisation group and the particular time point, and will be adjusted for baseline SF-36 scores, age, gender, diagnosis, smoking history, treatment and socioeconomic status. Intra-class correlation coefficients will be presented by group. The secondary analyses will compare deaths (overall and due to heart failure) using Kaplan-Meier estimation and the Cox proportional-hazards regression model, hospitalisations (overall and due to heart failure), NYHA stage, treatment, adherence, weight and obesity between the groups with longitudinal random-effects models described previously. Estimation methods developed by Verbeke and Molenberghs will be used to account for missing data (GPs and patients) [25].

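### Hospitalisations recorded over unequal visit intervals are sent to the linear score model, so if per-visit hospitalisations are the response, a constant rate effect can look delayed or accumulating

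*Protocol article*

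**What the plan says.** All references are to the protocol article.

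- **Data capture** (Instruments and outcomes): "Hospitalisations and mortality will be recorded by GPs at each planned visiting case report form".
- **Visit calendar** (Control group): "Their patients have the same schedule for visits as those in the intervention group (at 1, 4, 7, 10, 13, 19 months"). Both arms therefore share one calendar.
- **Model for hospitalisations** (Statistical analysis): the secondary analyses compare "hospitalisations (overall and due to heart failure), NYHA stage, treatment, adherence, weight and obesity between the groups with longitudinal random-effects models described previously".
- **What those models are** (same section): "Hierarchical linear regression models with random-effects levels for practice, individuals within practices and repeated measurements per individual (slope and intercept"), fitted to SF-36 and MLHFQ scores after baseline. The section adds: "These models will include an interaction factor between both the randomisation group and the particular time point".
- **Form of the outcome** (Instruments and outcomes): the secondary outcomes include hospitalisation, days in hospital and "the cumulative number of all cause death or HF hospitalizations and the cumulative number of days of hospitalisation". The article does not say whether the modelled hospitalisation variable is a yes/no event, a count per visit, a running total or a rate. It also does not say which visits enter the model.

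**The concern.** A questionnaire score describes the patient's state at a visit, and its meaning does not depend on how long ago the last visit was. A hospitalisation entry accumulates over the time since the last visit. The plan sends both to one model on the absolute scale, with a term that lets the group effect differ by time point.

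Month 19 is the time point of main interest and also closes the longest interval. If education lowered the admission rate by the same proportion from the start, per-visit counts could show the largest absolute difference at month 19. A reader could take this for a benefit that builds up or arrives late, when part or all of the pattern comes from the visit calendar. The Discussion says interpretation will rest on effect size and magnitude as well as significance, and magnitude over time is what would be distorted.

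**Working it through.** The article gives no design figure for hospitalisations, so there is none to reproduce.

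**Inputs**
- Visits at months 1, 4, 7, 10, 13 and 19 (Control group). From month 0 the intervals are 1, 3, 3, 3, 3 and 6 months.
- Rate ratio 0.76: assumed. It borrows the odds ratio for heart-failure hospitalisation quoted in the Background, as an illustration only.
- Control admission rate: not given. Assumed 0.05 per month (0.6 per patient-year), with 0.02 per month as a lower value.
- Both the rate and the rate ratio are held constant over 19 months.

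**Step 1: expected count per visit = rate × interval length**

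| Visit (month) | Interval (months) | Control | Intervention (× 0.76) | Difference | Ratio |
|---|---|---|---|---|---|
| 1 | 1 | 0.05 | 0.038 | -0.012 | 0.76 |
| 4, 7, 10, 13 | 3 | 0.15 | 0.114 | -0.036 | 0.76 |
| 19 | 6 | 0.30 | 0.228 | -0.072 | 0.76 |

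The difference per month is 0.05 × (0.76 - 1) = -0.012 in every interval. At 0.02 per month, all counts and differences are multiplied by 0.4.

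**Step 2: what a straight line in time would show**

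The mean visit month is 54/6 = 9. Deviations are -8, -5, -2, 1, 4 and 10, with sum of squares 210.
- Slope of the differences: [(-8)(-0.012) + (-5 - 2 + 1 + 4)(-0.036) + (10)(-0.072)]/210 = (0.096 + 0.072 - 0.720)/210 = -0.0026 per month.
- Mean difference: -0.228/6 = -0.038.
- Fitted difference at month 1: -0.038 + 8 × 0.00263 = -0.017. At month 19: -0.038 - 10 × 0.00263 = -0.064.
- Control slope: 0.552/0.24/210 = +0.011 per month.

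If time points are categorical, the step pattern of Step 1 appears instead of a line.

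**Step 3: other forms of the response, same assumptions**
- Any admission in the interval, 1 - exp(-rate × interval): risk differences -0.011, -0.032 (four times) and -0.055.
- Running total: differences go from -0.012 at month 1 to -0.012 × 19 = -0.228 at month 19.
- Interval counts pooled to the quality-of-life time points, months 7, 13 and 19 (intervals 7, 6 and 6): -0.084, -0.072 and -0.072, which is nearly flat.

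**Step 4: effect on the interaction test**

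A simulation used 40 practices × 5 patients per arm, overdispersed Poisson counts and 3,000 runs. It tested group-by-visit interaction on practice means with Hotelling's T², as a stand-in for the linear mixed model. The true rate ratio was constant throughout.

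| Control rate per patient-year | Rate ratio | Rejection, raw counts | Rejection, counts ÷ interval length |
|---|---|---|---|
| 0.5 | 1 | 5.0% | 4.8% |
| 0.5 | 0.76 | 9.7% | 5.1% |
| 0.5 | 0.5 | 36.4% | 4.7% |
| 1.0 | 1 | 4.0% | 4.6% |
| 1.0 | 0.76 | 13.8% | 5.0% |
| 1.0 | 0.5 | 62.4% | 5.1% |

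With no effect, raw counts do not inflate the error. With a constant effect, raw counts produce an apparent interaction, and dividing by interval length brings rejection back to about 5%.

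**The case against.** The strongest reply is that the problem depends on two things the article does not state: that the response is measured per visit, and that all six visits enter the model. Recording events on visit forms describes data capture, not the analysis variable. The score models were described for quality of life, for which "Quality of life is assessed at baseline and at 7, 13 and 19 months by the patients". If hospitalisations follow those time points as interval counts, the intervals are almost equal. **This stands**, and the point is therefore conditional. Yes/no responses at the six visits show a similar pattern, though, and a running total shows steady growth that choosing months 7, 13 and 19 would not remove.

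Three stronger readings are tempting, and the documents do not support them:
- *Counts and group differences grow steadily by construction.* For per-visit counts they do not: expected values are identical at months 4, 7, 10 and 13. The growth in Step 2 is a straight line drawn through two steps.
- *The calendar creates a false group difference.* It does not. Both arms share the schedule, so without a real effect the expected difference is zero at every visit.
- *A count model without an offset has the same fault.* On the log scale, interval length adds the same term to both arms. The common time trend is distorted, but the group ratio stays 0.76 at every visit.

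It can also be said that an offset is ordinary analysis-plan content and that its absence from a condensed article is no error. That is right for the offset alone. But the article does name a model, a linear one for scores, and a log person-time offset has no place in it. An analysis plan could cure this only by replacing the stated model.

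**Conclusion.** The point holds in a limited, conditional form. The article assigns an event outcome, recorded over intervals of 1 to 6 months, to a linear score model with a group-by-time-point interaction. If per-visit hospitalisations at the six visits are the response, a constant rate effect appears in the ratio 1:3:3:3:3:6 on the absolute scale and can be misread as delayed or accumulating. At rate ratio 0.76, the simulated chance of a significant interaction rises from about 5% to between 9.7% and 13.8%; at 0.5 it rises to between 36% and 62%. These sizes rest on assumed admission rates, a constant rate ratio and a proxy test.

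The consequence concerns how a real effect is described over time, not whether a false one is found. Hospitalisation is a secondary outcome that the Discussion already calls possibly underpowered. This is a modest correction, worth making because it is cheap.

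**What to change.** In the Statistical analysis section, take hospitalisations out of the list sent to the linear score models. For hospitalisations and hospital days, state one of the following:

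1. A log-link random-effects count model for each interval, allowing for overdispersion, with log person-time in that interval as offset and the practice and patient random effects kept. The group-by-time term then refers to rate ratios.
2. One 0-19-month rate per patient, using actual follow-up time, compared between groups with allowance for clustering by practice and without a time interaction.

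In either case, define the response and the time points, and count person-time only up to death or loss to follow-up.

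The cost is one or two sentences and a little extra analysis work. Person-time needs the dates of visits, deaths and losses. The article does not say these are on the case report forms, so this should be checked. No change to the design, sample size or primary analysis is needed.

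### As written, a linear model specified for quality-of-life scores is applied to count, ordinal and categorical secondary outcomes, and obesity is analysed where change in BMI is listed

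*Protocol article*

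**What the plan says.** The Statistical analysis section of the protocol article describes one random-effects model: "Hierarchical linear regression models with random-effects levels for practice", for individuals within practices and for repeated measurements. It is written for two instruments; the models "will be used to estimate the effects of the intervention on SF-36 and MLHFQ scores for the post-baseline time points". They contain a group-by-time interaction and "will be adjusted for baseline SF-36 scores, age, gender, diagnosis, smoking history, treatment and socioeconomic status".

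The secondary outcomes follow. Deaths get their own method: "The secondary analyses will compare deaths (overall and due to heart failure) using Kaplan-Meier estimation and the Cox proportional-hazards regression model". The same sentence then compares hospitalisations, for any cause and for heart failure, together with "NYHA stage, treatment, adherence, weight and obesity between the groups with longitudinal random-effects models described previously". No logistic, ordinal or count random-effects model is named anywhere in the article.

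The outcome list under Instruments and outcomes includes hospitalisation (all-cause and for heart failure), days in hospital, evolution of NYHA stage and of treatment, and "changes in weight and body mass index (BMI) at 19 months". The objectives at the end of the Background also give change in weight and BMI. Obesity is in neither list.

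**The concern.** The cross-reference in the secondary-outcome sentence has one antecedent, and that antecedent is linear. A linear mixed model assumes roughly normal residuals with constant variance and reports differences in means. Hospitalisations are counts, days in hospital are likely to be skewed, NYHA stage is ordinal, and treatment and obesity are categories. For these outcomes the variance changes with the mean, intervals can run past impossible values, and a mean difference in NYHA stage treats the step from I to II as equal to the step from II to III.

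The covariate list does not carry over either. It would adjust every secondary outcome for baseline SF-36 rather than for its own baseline, and it would put treatment on both sides of the equation when treatment is the outcome.

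Separately, the analysis names obesity for an outcome listed as change in BMI, and a category carries less information than the measurement.

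The effect measure matters here. The Discussion concedes that power may be too low for hospitalisations and other secondary outcomes, and says that interpretation will look at effect size and clinical magnitude as well as significance. Those estimates need a scale that suits the outcome.

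**Working it through.** **1. Outcome against model.** The article gives no figure to reproduce on this point, so the first check sets the outcome list beside the analysis sentence.

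| Outcome as listed | Type | Analysis as written | Fits? |
|---|---|---|---|
| Death | time to event | Kaplan-Meier, Cox | suits the type |
| Hospitalisation, days in hospital | count, skewed days | earlier random-effects model (linear) | no |
| NYHA stage | ordinal, entry at I to III | same | no |
| Treatment | categorical | same, with treatment also a covariate | no |
| Adherence | scale not given | same | cannot be judged |
| Weight | continuous | same | yes |
| BMI | continuous | not named; obesity named instead | mismatch |

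The analysis sentence does not mention days in hospital separately; they are placed here with hospitalisations.

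**2. Time at risk for hospitalisations.** Instruments and outcomes says GPs record hospitalisations at each planned visit. Visits are at 1, 4, 7, 10, 13 and 19 months, so the intervals are 1, 3, 3, 3, 3 and 6 months (total 19). If the model is fitted per visit, a patient who dies contributes no later intervals, and the time term absorbs the unequal interval lengths in the mean. Two things remain. The last interval before death or loss is only partly observed. Also, at a constant event rate (assumption) the 6-month interval has six times the expected count of the 1-month interval, and for Poisson counts six times the variance, so a single residual variance does not hold.

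**3. Does the linear model demonstrably harm the hospitalisation comparison?** A small simulation used 400 patients in 80 practices, skewed counts, 20% deaths, a true rate ratio of 0.6 and 120 runs per setting. The counts, deaths and rate ratio are assumptions, not figures from the article.

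- Power: 53% for the linear mixed model and 58% for a negative-binomial GEE with a time-at-risk offset. Monte Carlo standard error: √(0.53 × 0.47 / 120) = 0.046 and √(0.58 × 0.42 / 120) = 0.045. The 5-point gap is about one standard error of either estimate.
- Type I error: 0.05 and 0.07. Standard error at 0.05: √(0.05 × 0.95 / 120) = 0.020. Neither departs clearly from 5%.

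The simulation shows neither a loss of power nor inflation of type I error for the linear model.

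**4. Information lost if BMI becomes obese yes/no.** For a normal variable split so that a share p lies above the cut, the efficiency for a mean shift relative to the continuous analysis is φ(z_p)² / [p(1 − p)]. The article does not give the obesity share; 20% to 50% is assumed.

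- p = 0.20: 0.490
- p = 0.30: 0.576
- p = 0.40: 0.622
- p = 0.50: 0.637

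The split keeps about 49% to 64% and loses about 36% to 51%. This would be the real loss only if obesity were the sole analysis of body size. Weight is in the same sentence and is continuous. Height hardly changes over 19 months in patients over 50, so weight change carries nearly the same information as BMI change.

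**The case against.** The strongest reply is that the secondary-outcome sentence speaks of longitudinal random-effects models without repeating the word linear. The authors may have meant only the structure (practice, patient, repeated measures), with a suitable link for each outcome. The covariates support this, since nobody would knowingly adjust treatment for treatment. The section also separates variable types elsewhere, with Chi-square or Fisher tests for categorical variables and Cox regression for deaths. Link functions and offsets are, moreover, details that an article normally leaves to its analysis plan.

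Part of this stands. The charitable reading is possible, and the lack of an offset or link would not be a finding by itself. But the article does more than omit detail: it assigns these outcomes to a model it has described, and that model is linear. The Chi-square and Fisher tests do not fill the gap, because they ignore clustering by practice. If the treatment covariate means baseline treatment, it would be a sensible adjustment when treatment is the outcome, but the article does not say so.

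Three stronger readings are tempting and not supported:

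- *The linear model would give invalid or markedly weaker hospitalisation results.* The simulation does not show this, and per-visit recording handles much of the exposure problem.
- *About half the information on BMI is thrown away.* Weight remains continuous.
- *A dichotomisation of BMI is planned.* Binary obesity is an inference. No obesity outcome or cut-off is defined; the BMI threshold of 30 in Table 2 is a prompt for an education topic.

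**Conclusion.** Wrong as written, of low to moderate importance. Read literally, the Statistical analysis section applies a linear model built for SF-36 and MLHFQ scores, with their covariates, to count, ordinal and categorical outcomes, and it names obesity where the outcome list and the objectives name change in BMI. The cost lies in model fit and in the effect measure reported, not in a demonstrated loss of power or error control.

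The conclusion rests on taking the cross-reference at its word. If only the random-effects structure was meant, the point reduces to a clarification of wording plus the BMI mismatch. A reader might infer that the main result is at risk; it is not, because the quality-of-life model is not touched by this point.

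**What to change.** Keep the practice and patient random effects and state the model family for each outcome type:

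- Hospitalisations and days in hospital: a count model, for example negative-binomial, with log time at risk as offset, reported as a rate ratio.
- NYHA stage: a cumulative-logit mixed model.
- Binary treatment outcomes: a logistic mixed model.
- Weight and BMI: continuous, in the linear mixed model, as listed under Instruments and outcomes. Obesity should be at most supplementary, with its cut-off stated.

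Replace the carried-over covariates by the baseline value of the outcome analysed, where one is recorded. Where treatment is the outcome, do not use it as a covariate other than as that baseline value.

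The cost is a few lines of analysis wording and a little programming. No new data are needed, and the trial was ongoing at publication, so the change could be made before analysis.

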### Ethical considerations

The Institute’s ethics committee (Comité de Protection des Personnes Sud-Est I) approved the trial protocol on April 19th, 2010. The French drug agency, (Agence Nationale de Sécurité du Médicament et des produits de santé), gave its approval for the trial on March 5th, 2010 with the reference 2009-A01142-55. The study is conducted in compliance with the regulations on patient confidentiality (Comité consultatif sur le traitement de l’information en matière de recherche dans le domaine de la Santé (Advisory Committee on Data Processing for Matters of Research in the Field of Healthcare) and Commission Nationale de l’Information et des Libertés (National Commission for Data Protection) agreements under the reference 1223379). In compliance with the extended CONSORT statement for cluster, ETIC was registered on ClinicalTrials.gov as NCT01065142 [26].

## Discussion

ETIC is one of the few trials that involving only GPs [27]. Although multidisciplinary patient education programmes are probably more effective [28], the current healthcare organisation in France makes large-scale implementation of this type of intervention difficult, if not impossible. The idea behind ETIC is to evaluate a complex intervention including GP’s 2-day workshop and patient’s education programme in primary care in the current context of healthcare organisation in France to implement education into daily routine.

In Europe, most of the published trials regarding patient education programmes involve hospitalised or younger patients with a profile which is different from patients seen in primary care [29]. In a meta-analysis of randomised controlled trials involving patients with heart failure [30], the mean age of the patients was 61.4 years. In a recent Italian epidemiological study of primary care of patients with chronic heart failure, the mean age was 78.5 years [31]; our study population will probably have a comparable age.

In the ETIC trial, two different quality of life questionnaires are being used, one generic, the SF-36, and the other specific for chronic heart failure, the MLHFQ. The SF-36 questionnaire was chosen because the French version has been validated and it evaluates both physical and mental aspects of the quality of life, taking into consideration cultural differences [16,32]. The MLHFQ questionnaire was chosen because it is specific for patients with CHF, it is also validated in French and it accommodates psychometric properties [33]. In addition, it is recommended for initial use in clinical research [34], has been validated in primary care and is simple and fast to use [17].

The intervention in ETIC is novel because it is standardised with the topics generally used (clinical alarm signs, physical activity, diet and cardiovascular risk factors) [35], but it also involves a holistic approach, centred on the patients’ needs and feelings and taking into consideration their comorbidities and the representations of their disease [36]. The first and subsequent patient education sessions are based on, respectively, educational diagnosis and changes in habits, desires and worries about discussing specific topics, such as smoking habits [21,37].

For instance, one study on 240 patients with a mean age of 70 years and a majority of NYHA stage III (96.4%) reported baseline SF-36 mean scores of 45.1 in the intervention group and 46.8 in the control group [14]. The baseline MLHFQ mean scores were 42.5 and 42.6, respectively. In another study on 200 patients with a mean age of 63.5 years and a majority of patients with NYHA stage II-III (94%; 6% had stage IV), the baseline MLHFQ mean scores were 64.3 and 62.4 in the intervention and control groups, respectively [10]. In a study comparing home and hospital follow-up in 280 patients with a mean age of 71 years and slightly fewer patients with NYHA stage II-III (85%; 15% had stage IV), the baseline MLHFQ scores were 48.8 and 46.0, respectively [11]. In three other studies with 89%, 50% and 80% patients with NYHA stage III or IV, the mean MLHFQ scores were 49.3, 51.8, and 44.7, respectively [12,13,23]. Our patients will probably be older, with a better quality of life than the patients in all these studies because they are recruited in a primary care setting with NYHA stage I, II or III.

To our knowledge only one other cluster-randomised trial that measured the impact of a patient education programme by GPs has been published [23]. A total of 283 patients (mean = 76.3 years) were included: stage I – 1.8%; stage II – 7%; stage III – 38.9%; and stage IV – 50.5%. The mean MLHFQ score was 49.1 and 49.9 in the intervention and control groups, respectively.

The frequency of the visits in the ETIC trial, every 3 months, was similar to the standard of care; 87% of patients with heart failure meet their GP at least four times a year [38]. However, the educational aspects of the visits can be difficult for some of the GPs in the intervention group.

This study has limitations. The GP randomisation was done before the patient inclusions. The patients in the two groups might be different because the training received by the GPs in the intervention group may make them feel more competent and therefore, more inclined to include more severely ill patients. To avoid this bias, we could recruit randomised GPs after they had included their patients, using the ‘Zelen’ method [39]. Unfortunately, this has not been possible because the inclusion period lasts one year and the follow-up 19 months; regarding heart failure patient life expectancy, it would not be relevant [5].

GPs participating in this study might be interested in patient education and not be representative of French GPs. This bias is inherent in any study because GPs must volunteer to participate. Otherwise, it would be possible that the usual care group could modify their medical practice, due to the observation, which is known as Hawthorne effect [40].

The power of this study might be too low to detect differences in mortality, hospitalisations and secondary outcomes. Our interpretation will not focus only on statistical significance but on the effect size and the magnitude of improvement describing the clinical relevance [41]. Therefore, the statistical analysis plan includes multivariate analyses with adjustment for differences in the characteristics between the two groups.

In France, some studies have assessed the impact of patient education for CHF patients [7,8]. However, these interventions were delivered from multidisciplinary teams, associated in part with the hospital. This trial will provide insight in the effectiveness of a complex intervention including a GP’s 2-day workshop and patient’s education programme in the setting of a GP consultation to improve the quality of life in patients with chronic heart failure in a pragmatic approach. This complex intervention could be a CHF management tool for use during initial and further medical training.

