**Table 1 Tab1:** **Training seminar for general practitioners: 2-day workshop**

Module 1: Introduction	- Introduction to the concepts of the ETIC trial and patient education
Module 2: Heart failure	- Chronic heart failure: definitions; epidemiology; clinical diagnosis; treatment guidelines∗; echocardiographic criteria; cardiac biomarkers: B-type natriuretic peptide (BNP) and NT-proBNP (how, when to prescribe them, how to use them)
	- Clinical symptoms: how to recognize heart failure in daily practice?
	- NYHA stages: definitions, assessment of NYHA stages from case vignettes
	- Suspicious clinical signs
	- Adaptation of physical activity as a function of the NYHA stage
Module 3: Concepts of patient education	- Assessment and building on the patient’s previous knowledge
	- Identification of life-style and dietary habits, physical activity, hobbies, leisure activities, projects, and resources available to the patient
	- Assessment of the patient’s stage of change, motivation and attitudes
	- Collaboration with the patient to define achievable and measurable objectives
Module 4: Communication	- Communication skills
	- Communication tools
	- Motivational interviewing
	- Lifestyle counselling based on the 5As model (ask, assess, advise, assist, and arrange)
Module 5: Role-playing to simulate a patient consultation with the general practitioner	- Identification and use of the patient’s knowledge (clinical alarm signs, physical activity, diet and cardiovascular risk factors), values, motivation, projects and resources to implicate the patient in their personal objectives
	- Classification of the personal objectives by therapeutic priority and patient preference
	- Use of effective communication strategies
Module 6: Case report forms	- Inclusion and exclusion criteria
	- How to promote and present the ETIC trial to patients
	- How to fill in the case report forms
	- How to organize the follow-up and topics: educational booklet and educational tools (i.e. dietary leaflets, clinical alarm signs)

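### The covariate list omits baseline MLHFQ and NYHA stage, although the protocol names selection of sicker patients by intervention GPs as a possible bias

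*Protocol article*

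**What the plan says.** The limitations part of the Discussion states: "The GP randomisation was done before the patient inclusions". It then warns, in conditional wording (might, may), that their training could raise the confidence of intervention GPs and leave them "more inclined to include more severely ill patients". One way of preventing this is considered, a Zelen-type order ("To avoid this bias, we could recruit randomised GPs after they had included their patients"), and it is set aside: "Unfortunately, this has not been possible because the inclusion period lasts one year and the follow-up 19 months". Patient life expectancy is given as a further reason.

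Under Statistical analysis, the hierarchical models for SF-36 and MLHFQ at the post-baseline time points "will be adjusted for baseline SF-36 scores, age, gender, diagnosis, smoking history, treatment and socioeconomic status". The same section has a general clause: "If necessary, an adjustment to accommodate differences between the baseline characteristics of the groups will be made". The Discussion adds that the statistical analysis plan contains multivariate analyses adjusting for differences between the groups. Neither clause names a variable.

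The two arms prepare their GPs differently. Table 1 gives the intervention workshop material on recognising heart failure, on assessing NYHA stage from case vignettes, and on "How to promote and present the ETIC trial to patients". The Control group section describes a three-hour session on forms and eligibility criteria.

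**The concern.** GPs know their own arm from the training they receive, and they choose whom to invite. Randomising practices therefore does not by itself make the patients of the two arms comparable. The protocol sees this and says which way the imbalance might go: towards greater severity in the intervention arm. One would expect the fixed covariates to include the direct markers of heart failure severity at entry. The published list leaves out both.

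The gap is plainest for the MLHFQ. It is one of the two primary instruments and the one specific to heart failure. As worded, its model covers post-baseline scores only and adjusts for the baseline of the other instrument. The baseline MLHFQ is then neither response nor covariate. At stake are residual bias in the 19-month difference and some loss of precision.

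**Working it through.** **Does the list cover the named threat?**

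| Severity information at entry | Where it comes from | In the covariate list? |
|---|---|---|
| Baseline SF-36 | Instruments and outcomes | Yes |
| Diagnosis, treatment | Statistical analysis | Yes, but not defined |
| Baseline MLHFQ | Instruments and outcomes; first questionnaires are returned with the consent form | No |
| NYHA stage | Eligibility criterion; its change is a secondary outcome | No |

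Both missing items are available without new data.

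**The plan's own figures.** The point rests on no stated figure, but the scale comes from the sample size section: a difference of 12 points, effect size at least 0.6 (so SD at most 12/0.6 = 20), ICC 0.10 to 0.20, 40 practices × 5 = 200 patients per group, and 20% dropout of GPs and patients. At effect size 0.6, 90% power and 5% two-sided error, 59 per arm are needed. Times 1 + 4 × ICC (1.4 to 1.8), this is 83 to 107. After one 20% inflation it is 104 to 134, and after two it is 130 to 168. The stated 200 is not reproduced but is larger, so the plan is conservative here and this does not affect the point.

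**Crude bias.** Assumptions, not in the documents: NYHA III share 10 to 20 percentage points higher in the intervention arm; 10 to 20 MLHFQ points between stage III and stages I–II.

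- Bias = imbalance × score gap: 0.10 × 10 = 1.0 to 0.20 × 20 = 4.0 points.
- Relative to target: 1.0/12 = 8% to 4.0/12 = 33%.

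**After the planned adjustment.** Further assumption: 25% to 50% of the bias survives the listed covariates.

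- 0.25 × 1.0 = 0.25 to 0.50 × 4.0 = 2.0 points, or 2% to 17% of the target.

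**Consequence**, for a simple comparison of means with SD 20:

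- SE = 20 × √[(2/200)(1 + 4 × ICC)] = 2.37 (ICC 0.10) or 2.68 (ICC 0.20).
- Rejection rate when the true difference is zero = Φ(−1.96 − b/SE) + 1 − Φ(1.96 − b/SE). For b = 1 it is 7.1% or 6.6%; for b = 2 it is 13.5% or 11.6%, against a nominal 5%.
- Power for a true 12 points when the bias runs against the intervention = 1 − Φ(1.96 − (12 − b)/SE). For b = 2 it is 98.8% or 96.1%.
- With 200 × 0.8 × 0.8 = 128 per arm and 4 per practice, SE = 20 × √[(2/128)(1 + 3 × ICC)] = 2.85 or 3.16. Power at b = 2 is 93.9% or 88.5%. If all 4 points remained, it would be 80.1% or 71.6%.

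**The case against.** Four arguments on the other side carry weight.

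- **Severity is partly covered.** Baseline SF-36, diagnosis and treatment are in the model, and diagnosis may well separate reduced from preserved ejection fraction. This stands, and it is why the residual bias should be smaller than the crude figure. It does not give the MLHFQ model its own baseline. The reference to baseline SF-36 may be shorthand for the matching baseline score, but the text does not say so.
- **Other clauses could bring the variables in.** The if-necessary clause and the reference to the statistical analysis plan might do this. But they name nothing and depend on differences seen in the data, while the article does publish a fixed list. A choice made after an imbalance is seen is a weak remedy for a threat known beforehand.
- **Partial safeguards exist.** GPs are to take eligible patients in order, cardiologists confirm the diagnosis, NYHA IV is excluded, and patients do not know their GP's arm. These limit the problem. The cardiologist's letter confirms heart failure, not the order of selection.
- **NYHA is itself exposed.** No rater other than the GP is described, rating follows allocation, and only the intervention workshop is described as teaching staging. Adjusting for a covariate measured differently by arm can add bias. This stands, and it shapes the fix.

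A reader might go further and infer that the protocol predicts sicker intervention patients. It does not: its wording is conditional throughout. A reader might also infer that the design should still be repaired by having GPs list eligible patients before allocation is disclosed. Randomisation is already done and the trial is on-going, and not discussing every alternative to the Zelen order is no error.

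**Conclusion.** The point holds in a limited form. The protocol names a possible severity imbalance, and its stated covariate list omits the two most direct baseline measures of it, leaving the MLHFQ model without its own baseline. The correction for severity is therefore only partial.

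The size of the remaining bias is unknown. The crude and residual ranges shown rest wholly on assumed imbalances, score gaps and surviving fractions. The direction is also uncertain: sicker intervention patients would tend to score worse at 19 months, but regression to the mean could work the other way.

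It would be too much to conclude that the bias is likely to hide a 12-point benefit. With a 2-point residual bias, power stays at 88.5% or more in the cases worked. A residual bias matters more for the error rate and for the size of the estimate. Adjustment will not remove selection on unmeasured severity.

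**What to change.** Before allocation is known to the statistician:

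1. Name baseline MLHFQ as a covariate in the MLHFQ model. Patients or caregivers complete it, so it is less exposed to the difference in GP training.
2. Name baseline NYHA stage (I, II, III) as a fixed effect in the SF-36 and MLHFQ models.
3. Show the intervention effect with and without NYHA stage, because GPs trained differently in staging rate it after allocation.
4. Report baseline severity (MLHFQ, SF-36 and NYHA stage) by arm.

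The cost is two parameters for NYHA, one for baseline MLHFQ, and one sensitivity analysis. No new data are needed, and the sample size does not change.
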